#### 5.4.1 Preparation of Medication

A syringe adapter must be inserted into the bottle until it is aligned with the top edge of the bottle. An 1ml oral syringe is inserted into the opening of the syringe adapter. Before the syringe can be filled, the plunger of the syringe must be fully inserted into the syringe. The plunger of the syringe is carefully pulled out of the syringe until the liquid level inside the syringe reaches the desired value in ml on the 0,01-syringe scale. The bottle should be turned upside down for drawing up the solution. If bubbles appear in the solution during collection, the solution should be emptied back into the bottle and the collection repeated: for a good result, the syringe should be drawn up and back 5 times to remove air bubbles in the syringe. The full content of the oral syringe should be immediately, but slowly and gently, dispensed into the mouth of the patient. Care should be taken to ensure that the entire dose is administered. If an immediate administration of the prepared dose does not take place, the application syringe must be stored no longer than 24h at <25°C (best light-protected).

#### 5.5 Dosing

Sirolimus dosing recommendations vary among studies, depending on age of subjects and indications. Sirolimus has a narrow therapeutic window with considerable inter-individual pharmacokinetic variabilities. Most studies report median absolute doses of 2-2.5 mg daily (summarized in Overwater *et al.*, 2016, table e-1). Overwater and colleagues calculated a starting dose of 0.033 mg/kg once daily, based on the normal starting dose of 2 mg daily for an adult of >50kg body weight, initially targeting trough levels of 10-15 ng/ml, which had to be reduced to 5-10 ng/ml after the occurrence of two serious adverse events [42]. He *et al.*, by contrast utilize doses of 1mg/m^2 BSA once daily targeting trough concentrations of 2-10 ng/ml [36]. Almost all dosing recommendation for sirolimus in neonates and infants with indications other than TSC vary around 0.05-0.1 mg/kg or 0.5-1 mg/m^2 in line with our dosing scheme. The traditional fixed-dose stratification or weight-based dosing designs only control for a small part of the variable age-dependent metabolism of sirolimus, frequently leading to drug exposures outside of the targeted range [79]. Developmental changes over time in neonates and infants have a major impact on the pharmacokinetic-pharmacodynamic (PK/PD) profile of mTOR inhibitors such as sirolimus (e.g. age-dependent change in CYP3A activity) [80]. Sirolimus is extensively metabolized through CYP3A4 and CYP3A5 enzymes [81, 82] and there are several in vitro studies showing age-dependent changes in each hepatic CYP3A isoform expression [83, 84]. Emoto *et al.* described

the relationship between patient's age and allometrically size-normalized sirolimus clearance estimates by a sigmoidal  $E_{\max}$  model. They demonstrated the age-dependent trajectory of sirolimus clearance in neonates and infants after considering the effect of body size. They conclude that the developmental change in CYP3A expression is the most important factor for the age-dependent trajectory in neonates and infants [80]. An interesting report by Wang and colleagues used population pharmacokinetics and nonlinear mixed effect modeling to predict the optimal sirolimus dosing regimen in pediatric patients with TSC [85]. Based on data of 15 children between 1.08 and 13.95 years and designed to achieve target concentrations of 5-15 ng/ml, the authors recommend a starting dose of 0.1 mg/kg once daily for children between 5-10 kg body weight or 0.04 mg/kg twice daily for children between 5-20 kg body weight [85]. An important limitation to this study, however, is the absence of pharmacokinetic data from infants and children under 1 year of age, particularly considering the developmental differences in the activity of intestinal and hepatic drug-metabolizing enzymes and efflux transporters altering the bioavailability of drugs [86-88]. Driven by this motivation, Mizuno and colleagues used a similar prediction model to develop an age-appropriate sirolimus starting dose regimen for neonates and infants based on developmental changes in drug elimination capacity using 316 concentration measurements from 25 patients aged 0-4 years (15 of which were less than 2 years old). The trajectory of simulated sirolimus clearance increased with age. Mizuno proposed dosing regimens depending on age and body surface area and achieved target attainment of more than 75–95% across selected regimens [89]. The results are depicted in the following Figure 4 by Mizuno et al. [89].

Figure 4: Simulated sirolimus clearances compared with the estimated age-appropriate starting dosing regimens for the target range of 10–15 ng/ml

[figure not shown]

Based on the presented evidence, and in agreement with international TSC experts and our scientific advisory board, we believe that the model proposed by Mizuno *et al.* best serves this study since it includes pharmacokinetic data of infants/neonates, BSA and uses a twice daily (BID)

|                                                                    |                                              |                                |
|--------------------------------------------------------------------|----------------------------------------------|--------------------------------|
| Clinical Trial Code: PROTECT
EU trial number: 2022-502332-39-00 | Trial Protocol
(Version 06; (01.10.2024)) | Page 59 of 110
CONFIDENTIAL |
|--------------------------------------------------------------------|----------------------------------------------|--------------------------------|

regimen, which was shown to reduce absolute doses [89, 90]. To reduce the occurrence of AEs we will target trough levels of 5-10 ng/ml.

Table 4: Starting daily dose of IMP

| Age group (months) | Daily Dose (mg/m  /day) |
|--------------------|-------------------------------------|
| 0 - <1             | 0.5                                 |
| 1 - <2             | 0.6                                 |
| 2 - <3             | 0.74                                |
| 3 - <4             | 0.9                                 |

In general, the daily dose is divided into two administrations. In particular, a distinct dosing regimen will be used for neonates <4 weeks addressing the reduced excipient metabolism (see also sections “5.2.2.7 Excipients with known effect” and “5.4 Administration”): For neonates <4 weeks, the BID regimen will be maintained for daily volumes <0.2 ml, even for single volumes <0.1 ml. For infants ≥4 weeks receiving a daily dose <0.2 ml, administration is reduced to once daily in the morning to ensure dosing accuracy and switched to a BID regimen by the study team at the earliest timepoint possible. For infants ≥4 weeks receiving daily volumes <0.1 ml in the morning the administration will be every two days with the double daily dose to ensure dosing accuracy. Subjects randomized to the treatment group will receive oral sirolimus (Rapamune® oral solution) therapy. Sirolimus will be administered adapted to body surface area (BSA) with an age-dependent starting dose of **0.5 mg/m^2/day (0 - <1 months of age) to 0.9 mg/m^2/day (3 - <4 months of age)** divided BID, in addition to SOC.

The starting dose is calculated by the investigator by entering the patient's age in months, height in centimetres, and weight in kilograms into the eCRF. The system will calculate the appropriate starting dose. Rounding down on the discretion of subinvestigators for steps of 10µl will be accepted. The body surface area in m^2 will be calculated using the Gehan-George-formula: body surface area [m^2] = 0.0235 x height [cm]0.42246 x weight [kg]0.51456 [91].

#### 5.5.1 Maximum duration of treatment

Start of treatment at <4 months of age until 24 months of age. The maximum duration of treatment is 24 months inside the study.

#### 5.5.2 Maximum dose allowed

After the study drug has been started at the doses listed in, subsequent dosing will be individually adjusted informed by measurements of trough levels carried out at each study visit to reach target trough levels of 5-10 ng/ml.

#### 5.5.3 Dose modifications and interruptions

Two clinical trials in the United States (ClinicalTrials.gov: NCT05104983) and Poland (ClinicalTrials.gov: NCT04987463) are currently evaluating whether infantile-onset sirolimus

treatment can prevent/delay seizure onset in TSC. The following scheme for dose adjustments was established in collaboration with the study teams of the currently active trials in the US and Poland and is informed by previous experience in the use of sirolimus in this age group. No relevant AEs or overdosing occurred in the above-mentioned studies to date (as of 12/2022). Along these lines, in a previous study of patients with TSC-related seizures (EXIST-3 study), the investigators report that even twofold increases of normal everolimus blood levels did not significantly increase the risk of stomatitis or infections [92].

Table 5: Sirolimus dose adjustment

| Sirolimus trough levels (PK in ng/ml) | Required dose adjustment                                                                                                                    |
|---------------------------------------|---------------------------------------------------------------------------------------------------------------------------------------------|
| PK < 5                      | double all subsequent doses; additional telephone contact of trial site with caregiver(s) after 7 days +/- 2 days; repeat levels in 2 weeks |
| 5 ≤ PK ≤ 10                    | no adjustment                                                                                                                               |
| 10 < PK ≤ 15                | if no clinically significant AE or laboratory abnormalities occur, no dose adjustments; repeat levels in 2 weeks                            |
| 15 < PK ≤ 20                | reduce all subsequent doses to 75%; repeat levels in 2 weeks                                                                                |
| PK > 20                     | skip next dose, then reduce all subsequent doses to 50%; repeat levels in 2 weeks                                                           |

Legal guardian(s) should be informed by telephone or e-mail of dose adjustment by trial site as soon as laboratory results are available at trial site. Legal guardian(s) should be advised to contact the trial site if they did not receive a phone call or e-mail within 4 days after the last study visit.

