### Project 2. Assessment of response to vaccinations under treatment with IMP compared to SOC

Recently, mTOR inhibitors have been shown to enhance immune function and the response to vaccination (e.g. the influenza vaccine) at doses that were relatively well tolerated in the elderly [55, 56]. The impact of mTOR inhibitors on basic immunization in children has been insufficiently studied. Measurement of vaccination titers in the treatment group compared to the control group will assess differences in vaccination response and immunization. For this purpose, the titers of vaccines applied during the first year (measles, mumps, rubella, tetanus, pertussis, varicella; hepatitis b, polio) will be assessed in both groups.

To allow a detailed analysis of our cohort, standardized sample collection will be done longitudinally at two timepoints:

- Visit 8 (12 months of age) and Visit 12 (24 months of age).

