### 3. Clinical Trial Design

#### 3.1 Overall Trial Design

The clinical trial is planned as a two-armed, randomized, observer-blind, controlled phase IIb clinical trial for children <4 months of age at inclusion.

The treatment group will receive daily oral mTOR inhibitor (sirolimus) therapy in addition to standard of care (SOC), starting within the first 4 months of life. Sirolimus will be continued until the 2nd birthday when neuropsychologic testing will be done. The control group will receive SOC treatment only. Patients randomized to the treatment group will be followed closely with mandatory study visits at screening, start of treatment (V1), titration visits V2-V4 and at an age of 3, 6, 9, 12, 15, 18, 21 and 24 months for safety measures, to adjust sirolimus dosages following PK testing according to prespecified algorithms and to ensure compliance. In case neonates receive their first dose of IMP under the age of 4 weeks (corrected gestational age <4 weeks of life), caregivers will have up to two additional telephone calls by the study personnel up to the end of the 4th week of life. These calls will take place in those weeks where no titration visit takes place. An end-of-trial visit at 25 months of age will monitor safety parameters after end of trial. Subjects randomized to the control group will be treated according to SOC. No placebo will be administered to reduce the number of laboratory examinations at screening, 6 months, 12 months, and 24 months of age to the minimum required to control for laboratory abnormalities unrelated to the study intervention. Mandatory study visits for the control group are at screening and at 3, 6, 9, 12, 15, 18, 21 and 24 months of age. The enrolment in the primary study ends with the end-of-trial visit at age 25 months. Therapy of TSC manifestations according to SOC in both groups will not be affected by the trial. Seizure diaries, use of anti-seizure medications and concomitant medications, adverse events, vital signs (blood pressure, temperature, heart rate), height, body weight, OFC, and physical / neurological exam, and developmental milestones will be assessed at every visit. EEG and abdominal sonography will be done as described in chapter 6. Neuropsychologic testing will be performed at 12 and 24 months of age.

A schematic of the trial design is shown:

Figure 3: Schematic diagram of trial

[figure not shown]

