#### Vaccinations:

Sirolimus may affect the response to vaccinations. Sirolimus should be paused 14 days before until 14 days after receiving a live vaccine. The SmPC of sirolimus recommends avoiding live vaccinations during therapy. Individual risk/ benefits should be discussed with infectious disease specialists.

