#### Surgical interventions:

Treatment with sirolimus may affect wound healing. We recommend pausing treatment 14 days before until 14 days after elective surgical interventions. For non-elective interventions, therapy should also be paused until 14 days after the procedure.

Table 6: Sirolimus dose modifications for toxicities

This section is adapted from [23].

|                                                                                                                                                                       |                                                                                                                                                                                                                                                                                                                                                                                                                       |
|-----------------------------------------------------------------------------------------------------------------------------------------------------------------------|-----------------------------------------------------------------------------------------------------------------------------------------------------------------------------------------------------------------------------------------------------------------------------------------------------------------------------------------------------------------------------------------------------------------------|
| Non-infectious pneumonitis grade 2                                                                                                                                    | Interrupt study drug administration until resolution to $\leq$ grade 1. If resolution occurs within $\leq 4$ weeks, study drug should be re-started at the dose level prior to interruption. If resolution takes $> 4$ weeks, or if event recurs, hold study drug until recovery to $\leq$ grade 1 and reduce subsequent doses to 50%.                                                                                |

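### Table 5 doubles the sirolimus dose at any trough below 5 ng/ml, with no exception for one drawn in the first days after the protocol's own 28-day pause.

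*Protocol*

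**What the plan says.** Table 5 (section 5.5.3) lists the required dose adjustment for each trough band. Below 5 ng/ml the action is "double all subsequent doses; additional telephone contact of trial site with caregiver(s) after 7 days +/- 2 days; repeat levels in 2 weeks". Between 10 and 15 ng/ml it is "if no clinically significant AE or laboratory abnormalities occur, no dose adjustments; repeat levels in 2 weeks". Above 15 and up to 20 ng/ml, later doses are cut to 75%. No row depends on how long the child has been taking the current dose.

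The same section interrupts treatment on purpose. For vaccination: "Sirolimus should be paused 14 days before until 14 days after receiving a live vaccine". For surgery: "We recommend pausing treatment 14 days before until 14 days after elective surgical interventions". Neither paragraph gives a restart dose or a time for the first level after the restart, whereas Table 6 does give restart doses after toxicity.

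Live vaccines are foreseen. Project 2 in section 2.2.2 plans that "the titers of vaccines applied during the first year (measles, mumps, rubella, tetanus, pertussis, varicella; hepatitis b, polio) will be assessed in both groups". Trough levels are due at every study visit (section 5.4), and from V5 on the visits are tied to months of life. Section 3.1 describes the visits as serving "to adjust sirolimus dosages following PK testing according to prespecified algorithms".

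On the choice of target, section 5.5 reports that an earlier sirolimus trial in TSC was "initially targeting trough levels of 10-15 ng/ml, which had to be reduced to 5-10 ng/ml after the occurrence of two serious adverse events", and concludes: "To reduce the occurrence of AEs we will target trough levels of 5-10 ng/ml".

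**The concern.** A trough shows whether the dose is right only once the drug has accumulated again. After 28 days off treatment almost nothing is left, so for some days after the restart the level is low because of the pause and not because the dose is too small. Table 5 does not separate the two causes, and its action in this band is a doubling.

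The rules that might have separated them do not. The 14-day repeat sample (Table 1 footnote 14, sections 6.3 and 6.5) is tied to dose adjustments, and restarting the earlier dose is not one. The validity rule for troughs in section 6.8 concerns sampling immediately before dosing and is worded for the titration period. The re-initiation text after Table 6 asks for close clinical or laboratory monitoring, but names no sampling time and does not suspend Table 5.

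At stake is an infant on an immunosuppressant whose correct dose is doubled about two to three weeks after a live vaccine (14 days of pause after the vaccine plus 1 to 6 days), and who then stays above the range chosen for safety.

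**Working it through.** The plan gives no figure of its own on this point, so there is none to reproduce.

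**Inputs**
- Pause: 14 + 14 = 28 days = 672 h (section 5.5.3).
- Target trough C: 5-10 ng/ml (sections 5.4 and 5.5).
- Half-life h: section 5.2.2.5 gives 62 ± 16 h, in renal-transplant patients taking ciclosporin. The protocol gives no infant value. I use 46, 62 and 78 h, plus 24 h as a low case; all are assumptions for this population.
- Model (assumption): first-order washout and re-accumulation, restart at the pre-pause dose, trough proportional to dose, clearance constant over the weeks concerned.

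**Step 1: what is left after the pause.** Residual = 2^(-672/h), which is 0.05% at 62 h and 0.25% at 78 h.

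**Step 2: the reading t days after the restart.** Reading = C × f, with f = 1 - 2^(-24t/h). It falls below 5 when C < 5/f. At 62 h, f is 0.415 at 2 days, 0.658 at 4 days and 0.800 at 6 days. Pre-pause levels that read below 5 (ng/ml):

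| Days after restart | h = 24 h | h = 46 h | h = 62 h | h = 78 h |
|---|---|---|---|---|
| 2 | 5-6.67 | 5-9.71 | all of 5-10 | all of 5-10 |
| 4 | 5-5.33 | 5-6.54 | 5-7.60 | 5-8.71 |
| 6 | 5-5.08 | 5-5.64 | 5-6.25 | 5-6.93 |

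At 10 days the upper bound is 5.37 at 62 h (f = 0.932) and 5.67 at 78 h. At 14 days f is 0.977 and 0.950, giving bounds of 5.12 and 5.27.

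**Step 3: what Table 5 does next.** After doubling, the steady-state trough is 2C.
- C of 5 to 7.5 becomes 10 to 15. There is no adjustment, so the double dose stays.
- C above 7.5 and up to 10 becomes above 15 and up to 20. The cut to 75% gives 1.5 × C, about 11.3 to 15, and there it stays.

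Examples at 62 h, sampled 2 days after the restart: C = 7 reads 2.9, the two-week repeat reads 13.7, and the child settles at 14. C = 9 reads 3.7, the repeat reads 17.7, and after the cut the child settles at 13.5. The repeat level sees the rise but does not bring the child back to 5-10.

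**Step 4: how often a visit falls in this period.** The protocol gives no vaccine date, so these are counts of dates and not probabilities. For a vaccine on day L the restart is on day L + 14. With V8 held on day 365, the gap is 351 - L. A gap of 1 to 6 days needs L = 345 to 350, which is 6 dates. That is 6 of 92 (6.5%) if vaccination is spread over days 274-365, and 6 of 31 (19%) if it is confined to days 335-365. The restart day itself is left out: section 5.4 defines the level as a 12 h or 24 h trough, and on that day there is no preceding dose.

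**The case against.** The case against has real weight.

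- **Frequency.** A reader might infer that the pause makes the next trough low. It does not. With visits three months apart, the next sample can easily come later and be normal. Section 5.5.3 also notes that the product information advises against live vaccines during therapy, and refers the decision to infectious disease specialists.
- **Visit windows.** V8 has ±14 days. For the six counted dates the restart is on days 359-364 and V8 may be held as late as day 379, which is 15 to 20 days after the restart. Most other visits have ±7 days, which moves a sample from 1-6 to 8-13 days. At 8 days and 62 h only pre-pause levels of 5 to about 5.7 would be misread (f = 0.883).
- **Oversight.** Section 5.5.5 requires interruptions of 7 days or more to be discussed with the sponsor, and every 28-day pause qualifies. Section 5.5.2 describes dosing as individually adjusted and informed by trough levels, so a careful investigator may recognise the cause.
- **Harm.** The text just above Table 5 reports that even twofold rises in everolimus levels did not significantly increase stomatitis or infections. Table 5 tolerates 10-15 ng/ml on purpose. Section 5.5 also says that clearance increases with age, which would lower the level over time.
- **Half-life.** At 24 h the misread range at 4 and 6 days nearly vanishes.

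All of this limits how often the event occurs and how large it is. None of it removes the defect. No safeguard suspends the required doubling or tells a site to move the visit, and an investigator who sees the cause must depart from a required adjustment. The everolimus data concern another drug and did not change this trial's 5-10 target.

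**Conclusion.** The point holds as a gap in a stated rule. Followed as written, Table 5 doubles the dose of some children who were on target, if they are sampled in about the first 1 to 6 days after a protocol-directed pause, and then leaves them at about 10-15 ng/ml, which is 1.5 to 2 times their earlier exposure, unless a clinically significant adverse event or laboratory abnormality occurs.

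The size rests on the assumed half-life, on restart at the earlier dose and on the assumed vaccine dates. The event is uncommon, and the longer the half-life, the wider the misread range.

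Two stronger readings are not supported. One is that the pause rule and Table 5 contradict each other: both can be obeyed, and what is missing is the link between them. The other is that 10-15 ng/ml is shown to be harmful here: the protocol reports an earlier trial lowering that target after two serious adverse events, but also cites the everolimus reassurance. The titration phase is not the problem either, because the 14-day interval is stated there. The change is worth making because it is cheap and favours safety, not because many children would be affected.

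**What to change.** In the Vaccinations and Surgical interventions paragraphs of section 5.5.3, state that sirolimus restarts at the pre-pause dose. Add to Table 5 that a trough below 5 ng/ml drawn less than 10 days after a restart does not trigger an increase and is repeated at day 14 after the restart. State that reductions for high levels (Table 5) or toxicity (Table 6) apply at any time.

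Ten days matches the earliest permitted V2 (day 14 minus 4). By the day-14 repeat the level is about 98% of steady state at 62 h and 95% at 78 h, so only a child who was right at the lower limit of 5 could still read low.

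The cost is a wording change and, when a visit falls within 10 days of a restart and reads low, one extra appointment and PK sample (0.5 mL in section 6.8, 1-2 ml in section 6.5). A truly under-dosed child waits up to 14 days longer for an increase.

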| Grade 4 thrombocytopenia                                                                                                                                              | Interrupt study drug until recovery to $\leq$ grade 1. Then reduce subsequent doses to 50%.                                                                                                                                                                                                                                                                                                                           |
| Grade 2 neutropenia or anaemia                                                                                                                                        | No action                                                                                                                                                                                                                                                                                                                                                                                                             |
| Grade 3 neutropenia or anaemia                                                                                                                                        | Interrupt study drug until resolution to $\leq$ grade 1 or screening level. If resolution occurs $\leq 7$ days, reintroduce study drug at the dose level prior to interruption. If resolution occurs $> 7$ days, or event reoccurs within 28 days, reduce subsequent doses to 50%.                                                                                                                                    |
| Grade 4 neutropenia or anaemia                                                                                                                                        | Interrupt study drug until recovery to $\leq$ grade 1. Then reduce subsequent doses to 50%.                                                                                                                                                                                                                                                                                                                           |

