### 5.5.5 Subject Compliance

Compliance is measured by the amount of study medication left in the medication bottles at each study visit.

Subject compliance will be assessed at each visit during the trial and will be verified by interviewing caregivers and through accounting of returned trial medication at each visit and the patient diary kept by the caregiver(s). Compliance will be recorded by measuring the amount of sirolimus returned at each study visit. The person responsible for the clinical trial medication calculates the amount of used medication by subtracting the unused clinical trial medication (in ml) from the total contents of the study medication bottles and comparing it with the documentation of administered medication. The amount of the unused medication and the documentation should be reliable and consistent (with a tolerance of 15%). Details will be recorded in the eCRF.

Inadequately low levels (under the detection level of the laboratory) given the administered dose and not otherwise explicable, e.g. by interindividual rates of metabolization, should raise the suspicion for reduced compliance

Non-compliance (i.e., missed or incorrect dosing) will be documented in the source data and the eCRF. In subjects and / or caregiver(s) of the subject who demonstrate non-compliance between visit intervals, the caregiver(s) of the subject will be counselled by trial staff to address reasons for non-compliance. If after counselling the subject and / or caregiver(s) of the subject continues to exhibit non-compliance over two consecutive trial visits, the subject should be withdrawn from the trial. Dosing interruptions of 7 days or more must be discussed with the sponsor.

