## 6.3 Titration Visits

In case of any sirolimus dose adjustments, an additional pre-dose PK blood sample should be collected after two weeks, which during the beginning of the trial should coincide with the next regular study visit and after that during an additional appointment.

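### Tables 5 and 6 contradict each other after a 50% toxicity reduction: if the trough was below 10 ng/ml before the cut, Table 5 as written restores the pre-cut dose

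*Protocol*

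**What the plan says.** Table 5 (section 5.5.3) has an action column headed "Required dose adjustment". For a trough below 5 ng/ml the entry is "double all subsequent doses; additional telephone contact of trial site with caregiver(s) after 7 days" (give or take 2 days), with the level measured again at two weeks. The only row that takes adverse events into account is the one for 10 to 15 ng/ml: "if no clinically significant AE or laboratory abnormalities occur, no dose adjustments; repeat levels in 2 weeks". The row below 5 carries no condition.

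Table 6, in the same section, sets dose changes for toxicity. For grade 4 thrombocytopenia, neutropenia or anaemia the drug is held until recovery: "Then reduce subsequent doses to 50" per cent. Other grade 4 events not given their own rule, grade 4 transaminase elevation that resolves within 7 days, and grade 3 pneumonitis that resolves within 4 weeks also end in a 50% cut. Grade 2 pneumonitis, intolerable grade 2 or 3 mucositis, grade 3 transaminase elevation, grade 3 cytopenias and febrile neutropenia reach the cut only if they resolve slowly or recur; otherwise the previous dose is resumed.

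Section 6.3 adds: "In case of any sirolimus dose adjustments, an additional pre-dose PK blood sample should be collected after two weeks". Section 6.5 repeats the two-week sample and says sirolimus is dosed to reach 5 to 10 ng/ml. The pharmacokinetics paragraph of section 6.8 sends the site, once it has a trough, to section 5.5.3 as a whole. Section 5.5.2, on the maximum dose, names no ceiling; it says that "subsequent dosing will be individually adjusted informed by measurements of trough levels carried out at each study visit".

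**The concern.** Both tables are written as instructions, and the text never says which prevails when both apply. A child whose dose was halved for toxicity is likely to have a low trough at the next sample because of that cut. Table 5 reads the low trough as underdosing and doubles the dose.

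Three things are at stake. The first is safety: the children concerned have already had a significant event. The second is consistent conduct: one site may treat the Table 6 cut as binding while another follows Table 5, so similar children would receive different exposure. The third is the meaning of later decisions. Table 6 stops the drug if a grade 4 event recurs after a dose reduction, and under the doubling rule such a recurrence could be recorded when the child is no longer on a reduced dose.

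**Working it through.** The plan gives no figure for this to reproduce. The check follows the two rules in sequence.

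Inputs:
- Target trough 5 to 10 ng/ml (sections 5.5 and 5.5.2).
- Table 6 reduction: dose x 0.5.
- Table 5: below 5, dose x 2; 5 to 10, no change; above 10 and up to 15, no change unless there is a significant adverse event or laboratory abnormality.
- Next trough: two weeks after the adjustment (sections 6.3 and 6.5).
- Assumption: trough proportional to dose. The protocol supports this only from nonclinical data (section 5.2.2.4), so it is varied below.

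Step 1. Trough after the cut = 0.5 x pre-cut trough. New dose relative to the pre-cut dose = 0.5 x Table 5 factor.

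| Pre-cut trough (ng/ml) | After the cut | Table 5 action | Dose relative to pre-cut |
|---|---|---|---|
| 6 | 3.0 | double | 1.0 |
| 8 | 4.0 | double | 1.0 |
| 9.9 | 4.95 | double | 1.0 |
| 10 | 5.0 | none | 0.5 |
| 12 | 6.0 | none | 0.5 |
| 20 | 10.0 | none | 0.5 |

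Step 2. The cut is reversed when 0.5 x pre-cut trough < 5, that is, when the pre-cut trough is below 10 ng/ml. Within the target range only a trough of exactly 10 escapes.

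Step 3. Let r be the trough per unit dose after the cut divided by that before. The threshold becomes 5 / (0.5 x r):
- r = 1.0: 10.0 ng/ml
- r = 0.9: 11.1 ng/ml
- r = 0.8: 12.5 ng/ml
- r = 1.25: 8.0 ng/ml

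Section 5.5 reports that clearance rises with age. That pushes r below 1 and widens the affected group.

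Step 4. Would a two-week sample show the cut? Share of the new steady state reached at 14 days (336 h) = 1 - 0.5^(336 / half-life). Section 5.2.2.5 gives a half-life of 62 +/- 16 h, in renal transplant patients on ciclosporin rather than infants. At 46, 62 and 78 h the share is 99%, 98% and 95%. If that half-life is roughly right, the sample reflects the halved dose.

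Step 5. Is there an exit in the text? Table 5 has no exception below 5. Table 6 does not say how long a reduction lasts or whether a trough below 5 is then acceptable. Section 6.8 points to both tables without ranking them, and section 5.5.2 sets no ceiling. The paragraph closing section 5.5.3 allows re-initiation only if the event is judged unlikely to be related to the study drug. That is hard to square with Table 6, which prescribes a restart at 50% after toxicity.

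**The case against.** The strongest defence is that the protocol leaves room for judgement. Section 5.5.2 says dosing is informed by troughs rather than dictated by them. Sections 6.3 and 6.5 say the two-week sample should be taken, not that it must. Section 5.5.5 requires interruptions of 7 days or more to be discussed with the sponsor, which reaches many of the events that lead to a 50% cut. Section 7 lets the investigator stop the drug, and section 7.2 ends treatment on recurrent grade 4 events. These points reduce the likelihood of harm, but none tells a site what to do with a trough below 5 after a cut. Omitting the two-week sample would only postpone the question, because troughs are measured at every study visit.

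The number affected may also be small. In the series of 45 infants summarised in section 1.3.7, two grade 3 events (one ulcers/stomatitis, one abnormal blood count) clearly match Table 6 rows, and no grade 4 event was reported. 2/45 x 30 is about 1.3 treated children, before requiring slow resolution or recurrence. That series is only a rough guide to two years of treatment here.

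A reader might infer more than the documents support:
- That every toxicity reduction is undone. It is not: at pre-cut troughs of 10 to 20 ng/ml the cut stands (proportional case), and several Table 6 rows themselves resume the previous dose.
- That the restored dose is one shown to be toxic. The re-initiation clause, read literally, admits only events judged unlikely to be drug-related.
- That the doubling falls inside a 28-day recurrence window. In Table 6, recurrence within 28 days is a trigger for the cut, not a period of observation after it.
- That the same row conflicts with the compliance and pause rules. In section 5.5.5 the levels that "should raise the suspicion for reduced compliance" are those under the detection limit, not any level below 5. Adherence is checked at each visit, and the live-vaccine and elective-surgery pauses exceed the 7 days that call for sponsor discussion.

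**Conclusion.** The contradiction is real and limited in scope. For a child whose trough was below 10 ng/ml before a Table 6 reduction, the protocol as written calls for doubling at the two-week trough and so restores the full pre-cut dose. The boundary of 10 rests on trough being proportional to dose; it runs from 8.0 to 12.5 ng/ml over the range of r tested. The sequence is not endless for grade 4 events, since a recurrence leads to discontinuation, but that exit comes only after a second event. The case for correcting it rests on the safety of the individual infant and on uniform conduct across sites, not on any effect on power or on the primary analysis. It should be corrected before more children reach a Table 6 reduction.

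**What to change.** The sponsor should reconcile Tables 5 and 6 with each other and with section 5.5.2 (no ceiling), the re-initiation paragraph closing 5.5.3, section 5.5.5 (interruptions of 7 days or more), sections 6.3 and 6.5 (two-week trough), the pharmacokinetics paragraph of 6.8 and section 7.2 (permanent discontinuation). Section 5.5.3 should then state which instruction governs a trough below 5 ng/ml after a Table 6 reduction. The content of that rule is a clinical decision for the sponsor, and none is proposed here. The cost is a few sentences by amendment and a matching prompt in the eCRF. Sample size, endpoints and the primary analysis are unaffected.
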